## Abstract

**Background:**

Especially in the emergency setting, rapid and successful airway management is of major importance. Conventional endotracheal intubation is challenging and requires high level of individual skills and experience. Videolaryngoscopes like the C-MAC are likely to offer better glottis visualization and serve as alternatives to conventional endotracheal intubation. The aim of this study is to compare clinical performance and feasibility of the C-MAC videolaryngoscope compared to conventional endotracheal intubation in the emergency setting.

**Methods/Design:**

This study is designed as a prospective, patient-blinded, mono-center, randomized cohort study. This study will be performed at the Emergency Department of the University Hospital Zurich, Zurich, Switzerland. All patients transferred to the Emergency Department and requiring emergent endotracheal intubation will be screened. Successful intubation with first intubation attempt will serve as the primary outcome. Time to intubation, intubation attempts, Cormack & Lehane Score, ease of intubation, complications, necessity of using alternate intubation device, maximum drop of saturation, and potential technical problems serve as secondary outcomes.

**Discussion:**

In the clinical setting, the ultimate success rate of endotracheal intubation ranges between 97% and 99%. Unexpected difficulties during laryngoscopy and poor glottis visualization occur in up to 9% of all cases. In these cases, videolaryngoscopes may increase success rate of initial intubation attempt and thereby patient safety.

**Trial registration:**

www.clinicaltrials.gov (identifier NCT02297113).

## Background

Successful and rapid airway management is of major importance in the emergency setting and in specific situations life-saving. Beside a high level of expertise along with regular training and practice, successful endotracheal intubation sometimes requires additional tools to assist tracheal intubation [1-3].

Rapid Sequence Intubation (RSI) is indicated in all patients who are considered not sober and/or have an increased risk of gastric regurgitation and aspiration [4]. The main objective of this technique is to minimize the time interval between loss of protective airway reflexes and tracheal intubation with a cuffed endotracheal tube. This period is most critical, since aspiration of gastric content may to occur [5]. In the emergency setting, all patients are strictly considered not sober and RSI is obligatory indicated.

Videolaryngoscopy has been introduced to allow monitoring of conventional tracheal intubation and to assist during unexpected visualization difficulties of the glottis [6]. Recently a systematic review and meta-analysis clearly confirmed that videolaryngoscopy can offer better glottic views when compared with conventional direct laryngoscopy and therefore is an attractive option for the management of the unexpected difficult airway [7,8]. Thus, videolaryngoscopy has achieved an important role in the management of patients with unanticipated difficult or failed endotracheal intubation. The C-MAC videolaryngoscope is a relatively new device, already investigated in a wide range of clinical studies with promising clinical results [9-13]. However, its suitability in the context of RSI has not yet been studied so far.

### Specific aim of this study

The aim of this study is to investigate the initial success rate of endotracheal intubation with the C-MAC videolaryngoscopy compared with conventional direct laryngoscopy using Macintosh blade in an emergency setting. Additionally, we are going to compare primary and secondary outcome parameters in respect to feasibility and clinical performance of both intubation devices. Furthermore, we aim to evaluate potential technical problems and complications.

In particular we intend to test our primary hypothesis, that RSI using C-MAC is more successful at the first intubation attempt compared with conventional laryngoscopy intubation.

## Methods/Design

### Study design

This study is designed as a prospective, patient-blinded, mono-center, randomized cohort study. This study will be performed at the Emergency Department of the University Hospital Zurich, Zurich, Switzerland.

### Ethical approval

This study has been approved by the local ethic committee of the canton of Zurich (KEK Zurich, reference 2014--356, 31.october 2014) and has been registrated at www.clinicaltrials.gov (identifier NCT02297113).

### Patient population

150 adult patients of both gender, between 18 and 99 years, and requiring emergency RSI at the Emergency Department will be enrolled.

Patients will not be included in this study, if suffering from major maxilla-facial trauma, immobilized cervical spine or if there is any of the following conditions: Indication for awake fiberoptic guided intubation, ongoing Cardio-Pulmonary-Resuscitation (CPR), severe or immediately life-threating injury requiring immediately medical treatment or if patients is already included in any other ongoing clinical trial.

### Sample size calculation

Most available data are from patients with known intubation conditions and in an elective setting. This study focuses on RSI in an emergency setting and is therefore not comparable with other studies. In the emergency setting, the success rate at the initial intubation attempt is the most important clinical outcome parameter. Therefore, we assumed a success rate for the C-MAC intubation of 99% and a success rate for conventional laryngoscopy of 85%. We calculated an estimated total sample size of 144 (72 per group) with a power of 80% and an alpha level of 0.05. Because of potential drop out, we plan to include 150 patients in this study.

### Statistical analysis

Randomized groups will be compared for balance on baseline variables using traditional summary statistics and the standardized difference (STD), defined as the difference in means or proportions divided by the pooled standard deviation. Baseline variables with a STD > 0.20 will be considered imbalanced and will be adjusted for in all analyses. Randomized groups will be compared on outcomes with traditional statistical methods – t-test for normally distributed continuous outcomes, Wilcoxon Rank Sum test for ordinal or non-normal continuous data, and Chi-Square test for nominal variables. Data will be presented as mean with standard deviation, median and interquartile range, or number and percent. A p value < 0.05 is considered to be statistically significant. SPSS statistical software will be used for all analyses.

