### Allocation of patients

If fulfilling the in- and exclusion criteria, patient will be randomly assigned to one of two treatment groups:C-MAC videolaryngoscope in appropriate sizeConventional endotracheal intubation using Macintosh blade in appropriate size

Randomization (1:1) will be based on computer-generated codes maintained in identical, opaque envelopes that will be opened immediately before randomization.

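### Adjusting all analyses for any baseline variable with STD > 0.20 cannot be done with the tests the protocol names, so the primary test is undefined once chance flags a variable

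*Protocol article*

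**What the plan says.** The Statistical analysis section of the protocol article measures baseline balance by the standardized difference (STD), "defined as the difference in means or proportions divided by the pooled standard deviation". It then sets a binding rule: "Baseline variables with a STD > 0.20 will be considered imbalanced and will be adjusted for in all analyses". The next sentence assigns the outcome tests: the t-test for normally distributed continuous outcomes, then the "Wilcoxon Rank Sum test for ordinal or non-normal continuous data, and Chi-Square test for nominal variables". No adjusted counterpart to these tests is named, and the baseline variables to be screened are not listed or counted.

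The primary outcome (Measurements) is binary: success at the first intubation attempt. For the sample size, "we assumed a success rate for the C-MAC intubation of 99% and a success rate for conventional laryngoscopy of 85" per cent. The section continues: "We calculated an estimated total sample size of 144 (72 per group) with a power of 80% and an alpha level of 0.05". Enrolment is raised to 150 for drop-out, and allocation is 1:1.

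**The concern.** The rule covers every analysis, so it covers the primary one. A chi-square test has no place for a covariate, nor do the t-test and the rank sum test. As soon as one variable passes the threshold, the rule and the named tests cannot both be followed, and the document does not say what replaces the chi-square.

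Two features make this more than a drafting slip. First, in a randomised trial of this size the threshold is crossed often by chance, and crossing it says nothing about whether the variable predicts intubation success. Second, the planning assumptions imply very few failures, nearly all in one arm, and some common adjusted analyses behave badly in that situation. At stake is whether a true 14-point advantage is tested by the comparison the trial was sized for, or by an unspecified model that might miss it.

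**Working it through.** **Inputs.** From the protocol: threshold 0.20; success 99% and 85%; 72 per group calculated; 150 enrolled at 1:1, taken as 75 per arm; alpha 0.05. Assumed: a two-sided test, the STD read as an absolute value, and 3 to 15 independent baseline variables.

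**1. The planned sample size.** A two-sided, two-proportion calculation with continuity correction gives 72 per group, matching the protocol. Without the correction it gives 58. One-sided versions give 59 (corrected) and 46 (uncorrected). The trial was therefore sized as an unadjusted comparison of two proportions.

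**2. How often chance flags a variable.** Under randomisation the STD has standard error of about √(2/n). At n = 75 this is √(2/75) = 0.163, so 0.20 lies 0.20/0.163 ≈ 1.2 standard errors from zero. P(|STD| > 0.20) = 2 × (1 − Φ(0.20 × √(75/2))) = 0.221. At n = 72 it is 0.230.

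For k independent variables at 75 per arm, the chance of at least one flag is 1 − (1 − 0.221)^k:

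| Variables (assumed) | At least one flag | Expected number flagged |
|---|---|---|
| 3 | 53% | 3 × 0.221 = 0.7 |
| 5 | 71% | 1.1 |
| 10 | 92% | 2.2 |
| 15 | 98% | 3.3 |

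With a correlation of 0.3 between variables, the figures for 5 and 10 are 67% and 89%. If only positive differences counted, they would be 44% and 69%.

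**3. How much outcome information there is.** Expected failures are 75 × 0.01 + 75 × 0.15 = 0.75 + 11.25 = 12 (11.5 at 72 per arm). P(no C-MAC failure) = 0.99^75 = 0.47. With no failure in one arm, the treatment odds ratio in a maximum-likelihood logistic model has no finite estimate. In a simulation with two covariates, the Wald test rejected in none of these trials. Its power in flagged trials is therefore limited to roughly 1 − 0.47 = 0.53.

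**4. Power at 75 per arm under 99% versus 85%.** The unadjusted figures are exact. The others come from simulating the rule: chi-square if nothing is flagged, otherwise adjustment for the flagged variables.

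| Analysis | 5 variables | 10 variables |
|---|---|---|
| Uncorrected chi-square, no adjustment | 95% | 95% |
| Yates or Fisher, no adjustment | 89% | 89% |
| Rule with logistic model, Wald test | 59% | 49% (48% to 50% across runs) |
| Rule with logistic model, likelihood-ratio test | about 95% | about 95% |
| Rule with linear regression | 94.5% | 93.8% |

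The 59% can be decomposed. The rule triggered in 71.5% of simulated trials, where Wald power was 44.6%, contributing 0.715 × 0.446 = 0.319. The unflagged 28.5% contributed the other 0.586 − 0.319 = 0.267. The Wald figures barely changed when the covariates were made moderately prognostic (59% and 49%).

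**5. Type I error.** With 8% failures in both arms, simulated rejection rates were 3–4% (Wald), about 6% (likelihood ratio) and 5–6% (unadjusted chi-square).

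**The case against.** The strongest reply is that the large power loss belongs to one estimator, which the protocol never names. Linear regression, a likelihood-ratio test, or a Cochran-Mantel-Haenszel test stratified on the most imbalanced variable (about 94.5%) all keep power close to that of the plain chi-square. This stands, and the 59% and 49% may be quoted only with that condition.

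A second reply is that an article may leave the adjusted model and the covariate list to a full protocol or SAP. That is right as far as absence goes, and absence is not the point here. On a generous reading the named tests are defaults and an SAP supplies adjusted versions. Even then, the stated rule lets chance imbalance decide which analysis of the primary outcome is used and which covariates enter it, regardless of prognostic value.

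Three stronger readings are tempting, and the document does not support them:

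- **That the rule will almost always trigger.** This fits about 10 or more independent variables. The protocol gives no number, and with 3 the chance is 53%.
- **That the adjustment rule causes separation.** The 47% chance of an empty cell follows from the assumed 99% success. The unadjusted odds ratio would be infinite in the same trials, and the protocol does not name an odds ratio as its effect measure.
- **That choosing the analysis from the baseline table produces false positives.** The threshold and its consequence are fixed in advance, the trigger uses baseline data only, and the simulated type I error shows no material inflation.

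**Conclusion.** The concern holds in a limited form. The adjustment rule and the named tests cannot both be followed once a variable is flagged, which leaves the primary test undefined. A flag occurs by chance in about 22% of variables at 75 per arm. Whether at least one occurs is roughly even odds with 3 variables and very likely with 10, assuming independence.

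The cost in power ranges from about one percentage point with a suitable method to 36 points (95 − 59, 5 variables) or 46 points (95 − 49, 10 variables) with a Wald-tested logistic model. Against the Yates or Fisher figure, which is closer to how the sample size was calculated, the loss is 30 or 40 points. These figures rest on the protocol's own success rates, 75 analysed patients per arm and the assumed variable counts. The harm is an unfixed primary test that could lose power, depending on a choice not yet stated; it is not an excess of false positives.

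**What to change.** Remove the STD-triggered adjustment from the primary analysis. State that the primary analysis is the unadjusted comparison of first-attempt success between randomised arms, using the chi-square test already named (saying whether it is continuity-corrected), reported with a risk difference and 95% interval. Keep the STD as a descriptive measure in the baseline table.

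If an adjusted analysis is wanted, make it a sensitivity analysis with one or two prognostic covariates named in advance, fitted by a method that tolerates a zero cell, such as Firth-penalised logistic regression or a likelihood-ratio test. A single named adjusted method as primary would also remove the ambiguity, but it would depart from the comparison the trial was sized for.

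The cost is two or three sentences. Recruitment had begun when the article was submitted, so the change should be fixed and dated before outcomes are examined by arm. The downside is that a chance imbalance in an important variable would be handled in the sensitivity analysis and not in the headline result.

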### Clinical study procedure

All patients transferred to the Emergency Department suffering from severe, acute life-threaten disease or injury. All patients will be monitored including ECG, arterial blood pressure (non-invasive or invasive as appropriate), oxygen saturation (SpO_2_) and will follow standard operating procedures at our department. The bed of the patients will be stored head-up (about 30°). Anesthesia for RSI will be induced with fentanyl 1 to 2 mcg/kg body weight, propofol 1.5 to 3 mg/kg or thiopental 5 mg/kg body weight as clinically appropriate. Succinylcholine 1 mg/kg body weight or rocuronium 1 mg/kg body weight for neuromuscular blockade will be given. Complete muscle relaxation will be confirmed by absence of palpable twitches in response to supra-maximal train-of-four stimulation of the ulnar nerve at the wrist. The tracheal intubation will be performed by one of four highly-skilled researchers, trained in both intubation devices.

The blade-size of both intubation devices (Macintosh or C-MAC) as well as tube size will follow standard procedures at our department and is finally decided by the clinical assessment of the intubating researcher. This judgment is not affected by this study protocol.

The primary endpoint of this study is successful tracheal intubation, confirmed by proofing continuous end-tidal CO_2_ with continuous capnography. Further anesthesia management is independent of this study protocol and will follow standard operation procedure.

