#### Secondary outcome parameters

2.Time to intubation: defined as time between insertion of the blade into the mouth until detection of end-tidal CO_2,_ measured with integrated timer within the respiration system3.Total number of intubation attempts4.Cormack & Lehane score: as determined by intubation performing researcher5.Inadvertent esophageal intubation6.Ease of intubation (1–5) [14]: as determined by the intubation performing researcher (very easy, easy, somewhat difficult, difficult, impossible)7.Complications: diagnosed during and documented immediately after intubation procedure including violations of the teeth, injury/ bleeding of the larynx/ pharynx, and aspiration/regurgitation of gastric content8.Necessity of using further, alternative airway device for successful intubation (if randomized airway device failed)9.Maximum drop of saturation10.Technical problems with the device

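### Secondary outcomes are adjusted only on observed baseline imbalance, with no prespecified term for starting saturation or operator, which costs some precision but not validity

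*Protocol article*

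**What the plan says.** The Statistical analysis section of the protocol article states: "Randomized groups will be compared on outcomes with traditional statistical methods". It gives the t-test for normal continuous outcomes, then "Wilcoxon Rank Sum test for ordinal or non-normal continuous data, and Chi-Square test for nominal variables". Just before that it sets its only rule on covariates: "Baseline variables with a STD > 0.20 will be considered imbalanced and will be adjusted for in all analyses". The standardized difference (STD) is defined there for means or proportions. No covariate is named in advance.

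Under Clinical study procedure: "The tracheal intubation will be performed by one of four highly-skilled researchers, trained in both intubation devices". SpO2 is monitored in every patient. Under Secondary outcome parameters, the list includes time to intubation, "Cormack & Lehane score: as determined by intubation performing researcher", ease of intubation on a five-point scale ("as determined by the intubation performing researcher") and "Maximum drop of saturation". Allocation of patients describes 1:1 randomization and mentions no stratification by operator.

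**The concern.** Two sources of variation in the secondary outcomes are known in advance.

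- **Starting saturation.** The maximum drop is a starting value minus a lowest value, so the starting value has to be known. Comparing the drop directly fixes the weight on the starting value at one, whereas regression estimates that weight from the data.
- **Operator.** Four people perform all the intubations. The operator can affect time to intubation, and assigns the Cormack & Lehane and ease scores. Differences in speed or in use of the scale enter these comparisons as noise.

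The imbalance rule is a weak substitute for a prespecified term. It depends on how the randomization happened to fall, not on whether the variable predicts the outcome. A four-level operator factor has no single STD under the definition given. The Wilcoxon and chi-square tests, as named, cannot carry out the promised adjustment. What is at stake is the width of the intervals on feasibility and clinical performance, which the article lists among its aims.

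**Working it through.** **1. The plan's own figure.** The article gives a sample size for the primary outcome only: 99% against 85%, 80% power, alpha 0.05, 144 in total. With mean proportion 0.92 and difference 0.14, the two-sided formula gives

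n = [1.960·√(2·0.92·0.08) + 0.842·√(0.99·0.01 + 0.85·0.15)]² / 0.14² ≈ 57.8 per group.

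The continuity correction gives (57.8/4)·[1 + √(1 + 4/(57.8·0.14))]² ≈ 71.3, that is 72 per group and 144 in total. The figure reproduces, and nothing below changes it. The article gives no SD, correlation or power for any secondary outcome.

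**2. How often the STD rule would leave starting SpO2 unadjusted.** For one roughly normal baseline variable under randomization, the STD has standard error about √(2/n).

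- 72 per arm: 0.20/√(2/72) = 1.20, so P(|STD| > 0.20) = 0.23. It is left unadjusted 77% of the time.
- 75 per arm (all 150 patients): 0.20/√(2/75) = 1.22, so P = 0.22. It is left unadjusted 78% of the time.

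This supposes that starting SpO2 is counted among the baseline variables, which the article does not say.

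**3. Gain from ANCOVA on starting SpO2.** Let k = SD(start)/SD(lowest) and let r be the correlation between the two. Both are assumed. In units of the variance of the lowest value:

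- variance of the raw drop: 1 + k² − 2rk
- residual variance after ANCOVA: 1 − r²
- proportional reduction: (k − r)² / (1 + k² − 2rk)

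| k | r = 0.2 | r = 0.4 | r = 0.6 |
|---|---|---|---|
| 1 | 0.64/1.60 = 40% | 0.36/1.20 = 30% | 0.16/0.80 = 20% |
| 0.75 | 0.3025/1.2625 = 24% | 0.1225/0.9625 = 13% | 0.0225/0.6625 = 3% |
| 0.5 | 0.09/1.05 = 9% | 0.01/0.85 = 1% | 0.01/0.65 = 2% |

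The reduction is never negative, but it vanishes where r is close to k. Regressing the drop on the starting value gives the same treatment estimate as regressing the lowest value on it, apart from sign.

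**4. Gain from an operator term.** If operator explains a share R² of the variance (assumed), the residual variance is multiplied by 1 − R² and the interval width by √(1 − R²). With 72 per arm the unadjusted comparison has 80% power at (1.960 + 0.842)·√(2/72) = 0.467 SD. At that same difference:

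| R² | Interval width | Power | Equivalent total N = 144/(1 − R²) |
|---|---|---|---|
| 0 | ×1.000 | 80.0% | 144 |
| 0.05 | ×0.975 | 82.0% | 152 |
| 0.10 | ×0.949 | 84.0% | 160 |
| 0.20 | ×0.894 | 87.9% | 180 |

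Intervals therefore narrow by 2.5% to 10.6% for R² of 0.05 to 0.20. This is a linear-model approximation. It suits log time best and is only a guide for the ordinal scores.

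**5. Validity.** The unadjusted t-test was simulated with four operators, patients randomized individually, 72 per arm and 20,000 runs. Its type I error was 0.050, 0.053 and 0.051 at operator intraclass correlations of 0, 0.1 and 0.3.

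**6. Primary outcome.** A simulation with an assumed operator effect gave power 0.941 for the Pearson test and 0.939 for the operator-stratified (Cochran–Mantel–Haenszel) test. Without an operator effect, exact Pearson power at 72 per group is 0.942. Stratification gains nothing there.

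**The case against.** The strongest reply is that nothing here is an error. Two-sample tests in a 1:1 randomized trial are valid, and covariate lists are often left to an analysis plan, which is not shown. The first part stands. The second would settle the matter if the article were silent, but it states both the tests and the adjustment rule.

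Four stronger readings are tempting, and the documents do not support them.

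- *That the plan ignores starting saturation and operator.* It does not: any variable treated as baseline is adjusted for in all analyses once its STD exceeds 0.20. The fair criticism is of the trigger, and of named tests that cannot apply the adjustment.
- *That sharing four operators invalidates the tests.* Patients are randomized individually, and the simulated error rates stay close to 0.05.
- *That the trial already holds the data.* A starting SpO2 is needed to compute the drop. The article does not list the CRF items, so whether operator is recorded cannot be known.
- *That ANCOVA would cut the saturation variance by 20–40%.* This needs equal SDs at start and at the lowest point. Because saturation has a ceiling, starting values may well vary less, and the gain can then be close to nothing. The figure also compares linear-model variances and does not measure the loss from a Wilcoxon test on a skewed drop.

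It can also be said that four highly skilled operators, trained in both devices, may differ little. That stands too. The 5–20% share is an assumption, and the gain is zero if the share is zero.

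**Conclusion.** The point holds as a minor improvement in efficiency. Adjustment is tied to chance imbalance, so at 72 per arm starting SpO2 would be left out about 77% of the time, and no operator term is prespecified.

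The consequence is limited to the precision of secondary outcomes. For saturation, the variance reduction is 20–40% with equal SDs and about 1–9% if the starting SD is half that of the lowest value, for correlations of 0.2 to 0.6. For the operator-dependent outcomes, intervals narrow by about 2.5–11% if operator explains 5–20% of the variance. The documents supply none of these SDs, correlations or variance shares. Type I error, the primary comparison and the sample size of 144 are unaffected.

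**What to change.** Prespecify the following, independently of the STD rule:

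- **Saturation:** ANCOVA of the lowest SpO2 (or, equivalently, of the drop) on pre-induction SpO2, in a rank-based form if the data are skewed.
- **Time to intubation:** a linear model on log time with operator as a factor.
- **Cormack & Lehane score and ease:** a van Elteren test stratified by operator.
- **Data:** record the operator on the CRF if it is not already recorded.

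A Mantel–Haenszel analysis of first-attempt success by operator is optional as a sensitivity analysis and adds no meaningful power.

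The cost is a few sentences of analysis text, slightly more complex output and possibly one CRF field. No patients or procedures are added.
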